### Intervention

All patients in the GC group will be given methylprednisolone (MP) intravenously for 3 days after entering the ICU postoperatively. MP will be injected every 12 h with a tapering dosage (Fig. 2).

**Fig. 2 Fig2:**
[figure not shown]
Diagram of interventions

The first dose of MP will be given on the morning of postoperative day (POD) 1 at a dosage of 2 mg/kg/d, followed by another dose with the same dosage 12 h later. On POD 2 and POD 3, MP will be reduced to 1 mg/kg/d and 0.5 mg/kg/d respectively, with 12 h intervals between two injections.

All patients in the control group will receive treatments as usual without the administration of GC. Patients will be required to be supervised by medical personnel when administering the study drug, and their vital signs will be checked regularly in case of emergency.

Strategies to improve adherence to intervention and monitor adherence to procedures will be implemented. Three dedicated research fellows will screen all patients who enter the ICU after surgery. They will be responsible to check if certain candidate meets the study criteria. They will also be in charge of ensuring that intervention will be prescribed based on the protocol. In addition, two independent intensive care specialists will monitor adherence to interventions throughout the study period.

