## Statistics

### Sample size

In this study, the SOFA score will be monitored continuously for 4 days after surgery. Our primary hypothesis is that the reduction in SOFA score of patients who will be treated with GC postoperatively would be greater than that in those treated with normal care. Based on our previous study, a decline of 2.87 ± 1.69 between the baseline SOFA score on POD1 and the one on POD 3 was observed in our patients [17]. Assuming a 25% increase in the reduction of the SOFA score in the GC group, a test level of α = 0.1 (bilateral), and a test efficacy of (1-β) = 0.9, it is expected that 96 cases are needed in each group, for a total of 192 cases. An estimate of a 10% dropout rate in these groups indicates that a sample size of 212 cases will be required.

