There are a variety of strengths in our study. 1) The effect of GC in patients with aTAAD undergoing surgery is lacking, especially for those undergoing total aortic arch replacement with frozen elephant trunk implantation. Such a patient population is greatly exposed to the risk of SIRS and subsequent deterioration in organ function. This study will be the first RCT to investigate the role GC could play in these patients. 2) Former interventions of GC in cardiac surgery generally adopted a pulse regimen without tapering [7, 20]. The dosage of GC was particularly high (eg. 1 g MP) when given prophylactically before the initiation of CPB. However, benefits of GC to regulate dysregulated inflammation have mostly been observed in critical care studies adopting a mild-to-moderate dose of GC, as we have seen in inflammation-mediated conditions, such as acute respiratory distress syndrome [21–23]. In our study, we will implement an initial dosage of 4 mg/kg/d MP on POD 1 and taper it to 1 mg/kg/d on POD 3. Such a regimen will provide novel evidence on whether sequential and tapered use of GC would be better for patient prognosis. 3) A reduction in the SOFA is a reliable indicator of improvement in organ function and survival potential. Organ failure is one of the most prominent causes of death in surgical patients of aTAAD based on the data from international registry. Unfortunately, accurate definition of organ dysfunction is relatively missing, especially when multiple organs are involved. Previously, we have demonstrated that the SOFA score is associated with and could be used as a good predictor for all-cause in-hospital mortality and a lower SOFA score is linked to a decreased possibility of death after surgery, especially the one on POD 2 and POD 3 [17]. As our primary outcome would look at the difference between the SOFA score on POD 1 and POD 4, we believe such a choice could further elucidate the clinical value of the SOFA score. 4) Multiple biomarkers, such as CRP and IL-6, will be recorded in the research, which has the potential not only to depict a more accurate picture of inflammatory state in patients with aTAAD, but also to monitor and compare the effect of GC on inflammation as part of our secondary outcomes.

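### The methylprednisolone dose is stated two ways that differ twofold: 2 falling to 0.5 mg/kg/d in the Intervention section, 4 falling to 1 mg/kg/d in the Discussion

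*Protocol article*

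**What the plan says.** The Intervention section (Materials and methods) gives the duration as three days, with the drug "given methylprednisolone (MP) intravenously for 3 days after entering the ICU postoperatively", and the frequency as twice daily: "MP will be injected every 12 h with a tapering dosage". The paragraph after Fig. 2 sets the amounts. On POD 1 the first dose is given "at a dosage of 2 mg/kg/d, followed by another dose with the same dosage 12 h later". For the next two days it says: "On POD 2 and POD 3, MP will be reduced to 1 mg/kg/d and 0.5 mg/kg/d respectively, with 12 h intervals between two injections".

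The Discussion, in its second listed strength, contrasts the trial's regimen with earlier pulse regimens and says: "we will implement an initial dosage of 4 mg/kg/d MP on POD 1 and taper it to 1 mg/kg/d on POD 3". It gives no figure for POD 2.

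Both sections use the unit mg/kg/d. Nothing in the available text says that the Intervention figures are per injection. Fig. 2, which the Intervention section cites for the taper, is not available to this review.

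**The concern.** A figure in mg/kg/d is a daily total. On that reading the Intervention section orders 2 mg/kg on POD 1 and 0.5 mg/kg on POD 3, and the Discussion says 4 and 1. Both cannot be right.

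The Intervention text is also unclear taken alone. It attaches a per-day rate to a single injection and then repeats that dosage 12 hours later. The reader cannot tell whether 2 mg/kg is the injection or the day's total. The wording about repeating the same dosage appears only for POD 1, so POD 2 and POD 3 could be read differently from POD 1.

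The dose is the experimental treatment. If it is not fixed, three things suffer:

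- **Interpretation.** If patients in the glucocorticoid arm received different regimens, the estimated effect on SOFA could not be attributed to a defined dose.
- **Adherence.** The Intervention section relies on research fellows and two independent specialists to keep prescribing in line with the protocol. That check needs a single dose to check against. The per-protocol set in the Data analysis section is defined by complete data, not by dose received, so it would not separate patients given different amounts.
- **Safety.** Postoperative infection is a secondary outcome, and hyperglycaemia is monitored and corrected. A twofold uncertainty in steroid exposure bears on both.

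**Working it through.** **Inputs**

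- Intervention section: 2, 1 and 0.5, printed as mg/kg/d, for POD 1, 2 and 3, with injections every 12 h, so two per day.
- Discussion: 4 mg/kg/d on POD 1 and 1 mg/kg/d on POD 3.
- Body weight: not given. I assume 70 kg and show 60 to 80 kg.

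**Step 1. Can the Discussion's figures be reproduced from the Intervention text?**

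Taking the printed unit at face value, daily dose = printed figure:

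- POD 1: 2 mg/kg/d, against 4 in the Discussion. Ratio 4 / 2 = 2.0.
- POD 3: 0.5 mg/kg/d, against 1 in the Discussion. Ratio 1 / 0.5 = 2.0.

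They are not reproduced.

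Taking the printed figure as the amount per injection, daily dose = 2 × printed figure:

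- POD 1: 2 × 2 = 4 mg/kg/d. Matches.
- POD 3: 2 × 0.5 = 1 mg/kg/d. Matches.

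They are reproduced on both days, but only by setting the printed unit aside.

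**Step 2. Total exposure under each reading of the Intervention text**

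| Reading | POD 1 | POD 2 | POD 3 | Three-day total (mg/kg) |
|---|---|---|---|---|
| Figures are daily totals | 2 | 1 | 0.5 | 2 + 1 + 0.5 = 3.5 |
| Figures are per injection | 4 | 2 | 1 | 4 + 2 + 1 = 7 |
| POD 1 repeated, later days as printed | 4 | 1 | 0.5 | 4 + 1 + 0.5 = 5.5 |

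Only the second row agrees with the Discussion on both stated days. Its POD 2 value of 2 mg/kg comes from doubling the Intervention figure. It is not stated in the Discussion.

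**Step 3. In milligrams, for the first two readings**

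| Assumed weight | POD 1: daily total vs per injection | Three days: daily total vs per injection |
|---|---|---|
| 60 kg | 120 vs 240 mg | 210 vs 420 mg |
| 70 kg | 140 vs 280 mg | 245 vs 490 mg |
| 80 kg | 160 vs 320 mg | 280 vs 560 mg |

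**Step 4. Does the sample size depend on the dose?**

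No. Its inputs are "a decline of 2.87 ± 1.69 between the baseline SOFA score on POD1 and the one on POD 3" and a 25% larger reduction, 0.25 × 2.87 = 0.7175 points, at two-sided α = 0.1 and power 0.9. The usual formula n = 2(z₁ + z₂)²·SD² / Δ² gives 2 × (1.645 + 1.282)² × 1.69² / 0.7175² ≈ 95.0, which rounds up to the stated 96 per arm. The dose does not enter.

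**The case against.** The best defence is that there is one regimen with a mislabelled unit. The POD 1 sentence ties the figure to a single injection and then repeats it, and doubling every figure reproduces the Discussion on both days that can be compared. So 4, 2 and 1 mg/kg/d is probably what is meant. I accept that as the likely explanation. It does not dispose of the problem, because the section that staff would prescribe from then orders half the intended daily dose as printed.

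The Discussion is also a rationale, not a dosing instruction. Prescribing at a single centre, overseen by named trial roles, is unlikely to be taken from it. That is fair: mixed dosing is a possible consequence, and the document does not report it. But the oversight described in the Intervention section works from the same text that carries the conflict, so it does not resolve it.

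Fig. 2 or the full protocol may state the dose per injection. If so, bedside practice may be consistent. Even then, Fig. 2 can agree with only one of the two texts as printed, and the other needs correcting.

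Finally, the conflict leaves randomisation, endpoint definition, sample size and the choice of tests untouched. That is true. Its effect is on what treatment the comparison estimates, and on safety.

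**Conclusion.** The point holds. For the same drug, arm, days and unit, the Intervention section and the Discussion differ by exactly a factor of two on POD 1 and on POD 3, and at least one is wrong whatever Fig. 2 shows. Over three days the daily-total and per-injection readings of the Intervention text give 3.5 and 7 mg/kg.

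The factor of two between those readings rests on no assumption beyond two equal injections a day. The milligram figures assume a body weight. That the per-injection reading is the intended one is an inference, and this review does not say which dose is clinically right. Because the dose defines the treatment under test, this must be corrected.

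**What to change.** State the intended regimen once, giving for each of POD 1, 2 and 3 the mg/kg per injection, the 12-hour interval and the daily total in mg/kg. Use the same figures in the Intervention text, Fig. 2, the Discussion and the order set.

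If the higher regimen is intended, the Intervention text should read 2, 1 and 0.5 mg/kg per injection every 12 h, for daily totals of 4, 2 and 1 mg/kg. If the lower is intended, it should read 1, 0.5 and 0.25 mg/kg per injection (half of 2, 1 and 0.5), and the Discussion should say 2 mg/kg/d falling to 0.5 mg/kg/d.

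If any patients have been treated, check the doses they received against the clarified regimen and report any departures.

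The cost is a protocol correction or clarification letter and a check of the order set. No extra patients are needed and the sample size is unaffected.

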### Outcomes

The primary outcome will be the difference of Sequential Organ Failure Assessment (SOFA) score on POD 4 compared to baseline (on POD1 before MP administration).

Secondary outcomes will be in-hospital mortality, days of ICU stay; days of hospital stay; duration of mechanical ventilation; tracheotomy; continuous renal replacement therapy; postoperative infection; inflammatory markers on POD 1, 2 and 3; composite endpoint (in-hospital morbidity and mortality or ICU stay over 30 days or tracheotomy).

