### Overview

All patients with aTAAD undergoing surgery will be screened for study eligibility. Upon enrollment, eligible patients will be randomized 1:1 to one of the two treatment arms (i.e. GC or normal treatment) (Fig. 1). Data will be collected until hospital discharge or death.

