### Data analysis

This study will summarize patient disposition, demographic and other baseline characteristics, study drug exposure, safety and efficacy. Statistical analyses will be performed using R, version 3.5.0 (R Foundation for Statistical Computing, Vienna, Austria). Continuous variables will be summarized descriptively based on mean (Mean), standard deviation (SD), median (Median) and maximum (Max) and minimum (Min) values, and comparisons of differences between groups will be based on whether the data meet a normal distribution with a two independent samples t-test or wilcoxon nonparametric test. The categorical variables will be summarized descriptively based on the number of subjects in each category and their corresponding percentage share using the chi-square test, and the Fisher's exact test will be used to analyze the differences between groups if necessary. Kaplan–Meier curves and log-rank test will be used to estimate hospital survival in patients in both arms.

In addition, intention to treat analyses which will include all participants randomly assigned to the study arms regardless of their loss to follow-up or compliance will be implemented. Per-protocol analyses, which include all participants with complete data sets, will also be performed for primary and secondary outcomes. In case of missing data, multiple imputation will be calculated.

An interim analysis will be conducted when the set reaches 50% of the proposed number of patients; if the primary endpoint has been reached and differences exist, the data safety monitoring board will discuss and vote on whether to allow early termination of the study. Unless otherwise specified, α = 0.05 (two-sided test) and *p* < 0.05 was defined as statistically significant.

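### ICU days, hospital days and ventilation duration end at death, so an early death counts as a short stay; ranking deaths worst is a cheap improvement to three secondary outcomes

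*Protocol article*

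**What the plan says.** - **Outcomes** lists "days of ICU stay; days of hospital stay; duration of mechanical ventilation" as secondary outcomes, separate from in-hospital mortality. None is defined as free-days or restricted to survivors, and none assigns a value to death. The same list has a composite that contains death: "composite endpoint (in-hospital morbidity and mortality or ICU stay over 30 days or tracheotomy".
- **Data analysis** gives one rule for continuous variables, which depends on whether they look normally distributed: the arms are compared "with a two independent samples t-test or wilcoxon nonparametric test". Time-to-event methods are named only for survival: "Kaplan–Meier curves and log-rank test will be used to estimate hospital survival in patients in both arms".
- **Data analysis** also plans "intention to treat analyses which will include all participants randomly assigned to the study arms regardless of their loss to follow-up or compliance", so patients who die stay in the comparison.
- **Overview** sets the end of observation: "Data will be collected until hospital discharge or death".

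**The concern.** Taken together, these statements mean that a patient who dies on ICU day 4 enters the comparison with a 4-day stay. That patient ranks better than a survivor who leaves on day 7. A short duration can therefore mean recovery or death, and the test cannot tell them apart.

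This matters only if mortality differs between the arms. The Introduction describes the condition as one of high mortality, and the Discussion hopes that treatment may improve survival, so a difference is not far-fetched. If one arm has fewer early deaths, its stays can look longer for that reason alone. Testing survivors only would not solve this, because survival is itself an outcome of treatment and the groups compared would no longer be the randomised ones.

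**Working it through.** **Inputs from the document.** The planned total is 212 with 1:1 allocation, so 212 / 2 = 106 per arm. The general significance level is 0.05 two-sided. The plan gives no figure for the durations that could be reproduced.

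**Inputs that are assumptions.** The documents give no mortality rate, timing of death or distribution of stay. The illustration uses lognormal stays with log-SD 0.6 and a survivor median of 7 days in both arms. Mortality is 5% with glucocorticoids and 15% in control. The median time of death varies.

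**Step 1: expected difference in mean raw stay.** A lognormal mean is the median × exp(0.6²/2) = median × 1.197. Survivors' stays are the same in both arms, so

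glucocorticoid mean − control mean = (0.15 − 0.05) × 1.197 × (7 − median time of death).

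**Step 2: direction of the raw Wilcoxon.** This was simulated with 3,000 to 4,000 trials per setting.

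| Median time of death | Expected mean difference (days) | Raw Wilcoxon shows longer stay with glucocorticoids |
|---|---|---|
| 4 days | 0.10 × 1.197 × 3 = +0.36 | about 72% |
| 7 days | 0 | about 49% |
| 10 days | 0.10 × 1.197 × (−3) = −0.36 | about 35% |
| 14 days | 0.10 × 1.197 × (−7) = −0.84 | about 23% |

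The middle column shows why timing decides the sign: raw stay is shortened by deaths that come before survivors typically leave, and lengthened by deaths that come after.

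**Step 3: significance.** The second row of percentages above would mislead if read as error rates, since they count only the sign. With deaths at a median of 4 days, a significant result against the lower-mortality arm occurs in about 8–9% of trials, against 2.5% nominal in that direction. With mortality 10% against 15% it is about 5%.

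**Step 4: the same data with death ranked worst.** The time of death no longer enters, so the result does not depend on it. The test points the wrong way in about 10% of trials and is significant for the lower-mortality arm in about 24%. With mortality 10% in both arms, rejection is about 5% for the raw and the worst-rank test alike, so there is no cost in type I error.

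**Step 5: other assumptions.** With log-SD 0.7, deaths on days 1–4 and otherwise equal stays, the higher-mortality arm shows a significantly shorter raw stay in 2.3% of trials at 10% against 10% deaths, 7.5% at 10% against 15%, 18.6% at 10% against 20%, and 56.9% at 10% against 30%. If deaths fall evenly over days 1–30, the sign reverses: at 10% against 20%, the median is about 0.5 days longer in the higher-mortality arm.

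**The case against.** **The article only omits a coding detail.** It has one generic sentence on continuous variables, and a full protocol or analysis plan that is not shown may say how deaths count. Wilcoxon is also the test recommended here. That is fair as far as it goes. But the definition of the outcomes, the test, the population and the end of observation are all stated, and following them literally gives the result described. A rule for death elsewhere would settle the point.

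**Mortality is reported alongside.** In-hospital mortality, hospital survival and the composite would show an imbalance. This helps a careful reader, but it does not change what the three duration tests measure.

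**Very early deaths may be few.** The Inclusion criteria require a life expectancy above 3 days after surgery. This makes such deaths less likely without excluding them.

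**Stronger readings that a reader might infer.** One is that the planned test generally points the wrong way, or makes a harmful treatment look good. The documents do not support this: they give no mortality rate and no timing of death, and the sign reverses when deaths come late. Another is that 72% is the rate of wrong conclusions. It is only the sign of the difference, and significant wrong-way results are far rarer.

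**Conclusion.** The point holds as a modest improvement to three secondary outcomes. As written, ICU days, hospital days and ventilation duration mix early death with early recovery. If mortality differs, the comparison has no clear meaning and its direction depends on when patients die. In the illustration with early deaths and a 10-point mortality difference, significant results against the lower-mortality arm rise from 2.5% to about 8–9%. There is no such effect when deaths have the same median time as survivors' stays, and it reverses for later deaths. These sizes rest on assumed mortality, timing and stay distributions and are not predictions for this trial. If mortality is equal and deaths are timed alike in both arms, the raw test keeps its 5% error rate. The primary SOFA outcome and the sample size are not touched.

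**What to change.** Add one sentence to Data analysis: the three durations will be compared by the Wilcoxon test in all randomised patients, with in-hospital deaths ranked as the worst outcome. Report raw durations by arm, and by survival status within arm, as description only. Settle this before any unblinded look, including the interim analysis at 50%.

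The cost is small, since death and the durations are already collected and only a recode is needed. The downside is that the result then mixes death with duration, so it must be read beside in-hospital mortality.

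ICU-free, hospital-free and ventilator-free days to day 30, with death scored 0, are an alternative but not an equivalent. They tie a death with a survivor still in ICU, in hospital or on ventilation at day 30. They also need a stated assumption about readmission or death between discharge and day 30, because data collection ends at discharge.

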### ***Data to be collected*** (Table 1)

**Table 1 Tab1:** Data to be collected

Time Points	Day of ICU admission	Treatment					
		Preoperative	Pre-drug	24 h	48 h	72 h	Discharge or death
Enrollment	x						
Informed consent	x						
Inclusion and exclusion criteria	x						
Demographics^a^	x						
Past medical history^b^	x						
Pre-operative cardiac function^c^	x						
Operative information^d^	x						
Assessment							
Temperature		x	x	x	x	x	
Respiratory rate		x	x	x	x	x	
Heart rate		x	x	x	x	x	
Systolic blood pressure		x	x	x	x	x	
Diastolic blood pressure		x	x	x	x	x	
SOFA score	x			x	x	x	
Methylprednisolone administration				x	x	x	
Inflammatory indicators^e^		x	x	x	x	x	
Blood count^f^		x	x	x	x	x	
Blood biochemistry^g^		x	x	x	x	x	
Arterial blood gas^h^		x	x	x	x	x	
Concomitant medications^i^		x	x	x	x	x	
Adverse events^j^				x	x	x	x
24 h fluid intake and output		x	x	x	x	x	

*TIA* Transient ischemic attack, *COPD* Chronic obstructive pulmonary disease, *DM* Diabetes mellitus, *NYHA* New York Heart Association, *LVEF* Left ventricular ejection fractions, *TAPSE* Tricuspid annular plane systolic excusion, *ECG* Electrocardiogram, *ALICE* Albumin-indocyanine green evaluation, *ICU* Intensive care unit, *CCB* Calcium channel blockers, *CRP* C-reactive protein, *PCT* Procalcitonin, *ESR* Erythrocyte sedimentation rate, *TNFα* Tumor necrosis factor-α, *IL-6* Interleukin-6, *IL-10* Interleukin-10, *pH* potential of Hydrogen, *CRRT* Continuous renal replacement therapy

^a^age, sex, height(cm), weight(kg), smoking and alcohol consumption

^b^pre-existing definite preoperative diagnosis; previous or screening period medical history (including at least hypertension, TIA, COPD, stroke, DM, various arrhythmias, peptic ulcer)

^c^preoperative NYHA classification, preoperative cardiac ultrasound including LVEF, TAPSE, preoperative ECG, myocardial enzyme profile, preoperative ALICE score for entrapment

^d^name of the procedure, duration of the procedure (min), time outside the body (min), time of block (min), time of transfer to the ICU. Intraoperative dose and time of hormone use, blood loss, and transfusion volume; β-blockers, CCB, anticoagulants such as aspirin, antiplatelet agents, antihypertensive agents, cardiotonic agents, proton pump inhibitors or H2-blockers, antibiotics used within the previous 7 days

^e^CRP, PCT, ESR, TNFα, IL-6, IL-10

^f^hemoglobin, white blood cell, neutrophil count, lymphocyte count, platelet count

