### Subgroup analyses

The effect of the treatment among different subgroups: (1) gender, (2) diabetes, (3) The European System for Cardiac Operative Risk Evaluation (EuroSCORE) II, (4) Cardiopulmonary Bypass (CPB) duration, (5) age, (6) high sensitivity C-reactive protein on POD 1 and (7) SOFA on POD 1 will be analyzed. Stratified analysis using a logistic regression or Cox proportional hazards model, as applicable, will be performed. By adding a product term to the model that already contains the treatment and the subgroup factor, the interaction between each subgroup factor and the treatment group will be tested.

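### The inflammatory-marker outcome (POD 1, 2 and 3) does not match the sampling schedule: on the better supported reading it includes the pre-dose sample and omits the scheduled 72 h sample

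*Protocol article*

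**What the plan says.** - **Outcome.** The Outcomes section names "inflammatory markers on POD 1, 2 and 3" among the secondary outcomes.
- **Baseline.** The same section measures the SOFA change "compared to baseline (on POD1 before MP administration", with POD 4 as the endpoint. This baseline is defined for SOFA only.
- **Dosing.** Under Intervention, "MP will be injected every 12 h with a tapering dosage" for three days. "The first dose of MP will be given on the morning of postoperative day (POD) 1", and "On POD 2 and POD 3, MP will be reduced to 1 mg/kg/d and 0.5 mg/kg/d respectively".
- **Subgroups.** The Subgroup analyses section lists "6) high sensitivity C-reactive protein on POD 1 and (7) SOFA on POD 1 will be analyzed", so POD 1 CRP stands beside POD 1 SOFA as a baseline factor.
- **Schedule.** Table 1 has marker samples preoperatively, pre-drug and at 24, 48 and 72 h. Its MP administration row is marked at 24, 48 and 72 h and not at pre-drug. No column carries a POD number.
- **Data entry.** Data collection and storage covers POD 1 through POD 4, then discharge.
- **Analysis.** For continuous variables, Data analysis gives a two-sample t-test or a Wilcoxon test. It states no baseline adjustment or change score for the markers.

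**The concern.** The Discussion presents the markers as the means of comparing the effect of glucocorticoids on inflammation, and this is the only declared outcome that does so. Its time points should therefore be samples on which treatment can act, and should include the one taken when the course is complete.

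If POD 1 means the pre-drug sample, the POD 1 value cannot carry a treatment effect, and the same CRP value serves both as an outcome and as a subgroup factor. The 72 h sample is drawn at the time of the primary endpoint but is not declared. Adding it after the data have been seen would be post hoc.

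**Working it through.** **1. The plan's own figure.** No figure is stated for the markers. The only design figure is the SOFA sample size, and it reproduces. With a difference of 0.25 × 2.87 = 0.7175, SD 1.69, two-sided alpha 0.10 and power 0.90, n = 2 × [1.69 × (1.645 + 1.282) / 0.7175]² = 95.02, so 96 per group. The point below does not depend on it.

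**2. Hours against POD numbers (reading A).** Take the POD 1 morning dose as hour 0, with injections at about 0, 12, 24, 36, 48 and 60 h. Assume each sample is drawn just before that morning's dose. The stated daily doses are in the ratio 2 : 1 : 0.5, total 3.5.

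| Table 1 column | POD | Injections given | Share of cumulative dose | Declared outcome? |
|---|---|---|---|---|
| Pre-drug | 1 | 0 of 6 | 0 / 3.5 = 0% | yes |
| 24 h | 2 | 2 of 6 | 2 / 3.5 = 57% | yes |
| 48 h | 3 | 4 of 6 | 3 / 3.5 = 86% | yes |
| 72 h | 4 | 6 of 6 | 3.5 / 3.5 = 100% | no |

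The shares are the same whether the stated doses are per injection or per day, because only the ratio enters.

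**3. Support for reading A.** Four postoperative marker samples match the four days of data entry, POD 1 to POD 4, one to one. The first dose is on the morning of POD 1. The SOFA baseline is POD 1 before MP, and CRP on POD 1 is grouped with it as a subgroup factor. With 72 h as POD 4, Table 1 also contains the SOFA assessment that the primary outcome needs.

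**4. The other reading (reading B).** The MP administration row is marked at 24, 48 and 72 h, and dosing is on POD 1, 2 and 3. Those columns can therefore be read as the three treatment days. All three declared time points are then post-dose, the 72 h sample is included, and neither defect arises. The labels would still disagree: POD 1 would mean pre-drug for the SOFA baseline but post-dose for the marker outcome, and Table 1 would show no SOFA labelled POD 4. The administration row also fits reading A if each column records the preceding 24 h.

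**5. What a stand-alone POD 1 test would deliver under reading A.** With 96 per group and two-sided alpha 0.05, the rejection probability for a standardised difference d is 1 − Φ(1.96 − d√48) + Φ(−1.96 − d√48).

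- d = 0, which holds before any dose: 0.05.
- d = 0.3 (assumed): 0.55.
- d = 0.5 (assumed): 0.93.

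At POD 1 only the first line can apply. Table 1 lists six markers ("e^CRP, PCT, ESR, TNFα, IL-6, IL-10"). Six independent stand-alone tests would give at least one false difference with probability 1 − 0.95⁶ = 0.265. This is an upper bound, since the markers are biologically related. The list in the text omits ESR, and five markers would give 1 − 0.95⁵ = 0.226.

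**The case against.** The strongest reply is that the mapping is inferred. The pre-drug baseline is explicit for SOFA only, no hour is given for a POD 1 marker sample, and the administration row permits reading B, under which the outcome is sound. The SOFA row is also a weak witness: as extracted, its first mark is under the day of ICU admission and it has none at pre-drug, so it fits the stated baseline poorly on either reading. A 72 h assessment that closes the third treatment day would in any case fall at about the morning of POD 4. And under reading B the separate pre-drug sample could still supply the CRP subgroup factor. This stands as a limit on certainty. It does not remove the need to reconcile the labels.

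A second reply is that a baseline value in a serial outcome is ordinary, as a reference for change or the first point of a series, and that a separate analysis plan may say so. This also stands. A reader might infer that one of the three time points is null by design, but that is true only of a stand-alone POD 1 comparison under reading A, and the article does not say that one will be made.

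Two further inferences are tempting and not supported:

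- **That the full course is never tested.** The 72 h sample is scheduled and can be analysed, and the 48 h sample already follows about 86% of the cumulative dose.
- **That SOFA and marker results cannot be lined up.** Table 1 schedules both at 24, 48 and 72 h. What is missing is the declaration of the 72 h markers as an outcome.

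**Conclusion.** The point holds as a mismatch between the declared outcome days and the sampling schedule. On the better supported mapping, the secondary outcome includes one pre-treatment time point out of three. It leaves out the only sample taken after all six injections, which is also the one concurrent with the primary endpoint. This rests on two assumptions: that the POD 1 marker sample is the pre-drug one, as for SOFA, and that samples are drawn before the morning dose. On the other reading only the labelling conflict remains.

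The consequence is limited to one secondary outcome. The primary outcome, its analysis and the sample size are unaffected. The correction is still worth making, because it uses data already scheduled, fixes the 72 h comparison in advance, and improves on the unadjusted tests under either reading.

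**What to change.** - **Define the outcome by hours from the first dose:** inflammatory markers at 24, 48 and 72 h, compared between arms with the pre-drug value as a baseline covariate, on a log scale if the marker is skewed. If ρ is the correlation between the pre-drug and later values, adjustment multiplies the residual variance by about 1 − ρ², so in samples of this size it loses almost nothing when ρ is near zero and gains otherwise.
- **Give the pre-drug POD 1 value one role:** baseline characteristic, covariate and subgroup factor, not outcome.
- **Label Table 1's columns with both hours and POD number,** so that Outcomes, Table 1 and Subgroup analyses agree.
- **Date the change** before marker data are examined by arm.

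The cost is a few lines of wording, with no extra blood draws or patients. One practical caution: the Discussion expects some stable patients to leave the ICU within three days, so 72 h values may be missing more often in those patients. The multiple imputation already named in Data analysis should be stated to cover these values.
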